### Study settings and participants

This is a multisite study conducted in collaboration with the palliative care teams from three regional hospitals. In-hospital patients with ESHF are reviewed by the physicians, and patients who are seen to be not benefiting from active medical treatment are considered for palliative care. The general inclusion criteria for subject recruitment include the ability to speak Cantonese, living within the hospital service area, and the ability to be contacted by phone. Specific inclusion criteria are based on the National Gold Standards Framework, Prognostic Indicator Guidance 2008 [51], in which patients must fulfill at least two of the indicators: (i) HF with New York Heart Association stage III or IV, (ii) patient thought to be in the last year of life, (iii) repeated hospital admissions with symptoms of HF, (iv) existence of physical or psychological symptoms despite optimal therapy. The nurse who is responsible for recruitment identifies eligible subjects, and the physician confirms that the patient fulfills the specific criteria and refers him/her to the PC team. Those with cognitive impairment, diagnosed with severe psychiatric disorders in their medical record, or discharged to a nursing home or other institution are excluded.

### Recruitment procedures

The ESHF patients who fulfill the set criteria are placed on the palliative care pathway. The research team approaches the patients for subject recruitment. A written consent form is signed if patients agree to participate in the study. After obtaining written informed consent, a research assistant who is blinded to the treatment assignment conducts a baseline interview, including participants’ demographic data. The self-rated measures adopted in this study are detailed in the outcome measures section below.

### Randomization and blinding

Randomization in permuted blocks is used. The permuted block randomization scheme was generated by computer software at www.randomization.com [52]. Randomization is done by an independent research team member who is not involved in any other parts of the study, in order to guarantee allocation concealment. The group assignment is placed in a sealed envelope, which is retained by the site investigator, who has no connection with the clinical team. Having successfully recruited a subject, the research nurse calls the independent site investigator to open an envelope and assign a group code to the participant according to the randomization scheme. The independent site investigator is blinded to the meaning of the group code. The participants and family members need to be introduced to the intervention program and they are not blinded. The intervention nurses are also not blinded since they need to deliver the intervention. Only the research assistants who help to collect the data are blinded to the group assignment.

### Study intervention

#### Usual care

Participants in both groups receive customary hospital-based care, which is a palliative care consultation service. The service includes communication on diagnosis, prognosis, advance care planning, symptom assessment, and caregiver support by a palliative physician or nurse. Home visits and telephone calls may be provided as part of the customary service if deemed necessary, and the number of visits and calls provided will be recorded for reference in the final analysis.

#### Usual care plus HPHP

In this group, the Home-based Palliative HF Program (HPHP) is initiated and supported by a core multidisciplinary palliative care team. The composition of the core team includes a palliative care nurse who acts as a nurse case manager (NCM), a palliative specialist, a social worker, and a group of trained nursing students as volunteers. The effect of using volunteers adds value, as shown in a local study [42] and elsewhere [53, 54]. The HPHP was developed based on the six principles for palliative care and the four-Cs transitional model, and as described in the conceptual framework section. Structured and regular home visits and telephone calls are two common approaches that can bring about positive effects in transitional care [23, 42, 50, 55, 56]. The comprehensive package of care will be guided by evidence-driven protocols formulated by the research team.

Below are the descriptions of the protocols.Protocol for home visits – The first visit will be jointly delivered by the NCM and nursing students. Subsequent monthly visits will be conducted by the NCM or nursing students separately. The NCM will follow up on the health problems identified in the pre-discharge assessment in the first home visit. The subsequent home visits will follow up on the issues and goals of the previous visit. The nursing students will focus on social issues and report to the NCM and social worker after each home visit. The NCM will help set mutual goals with the patient to enhance optimal symptom control as well as social, psychological, and spiritual well-being. The NCM will consult the physicians in palliative care for clinical decisions, if needed. All home visits will be documented on structured forms designed based on the Omaha System [57]. The Omaha System was originally used in the United States. In Hong Kong, the research team has used it and found it comprehensive and valid for use with community-dwelling patients, including medical and hospice groups [29, 42, 49].Protocol for telephone follow-up – The NCM will initiate calls between home visits to monitor progress, provide health advice, reinforce appropriate health behavior, assess the need for referral, and review management goals with the patients. The Omaha System will continue to be used as a framework to guide practice and documentation.Protocol for referral system – A referral protocol will be established in case patients’ needs require further help, including: (a) social services – social, psychological, and financial support; (b) pastoral service – spiritual support; (c) medical clinic – medical review, drug adjustment; (d) nurse clinic – health assessment, non-pharmacological measures of symptom control; (e) emergency room – urgent conditions.Protocol for patient-initiated calls – Besides provider-initiated home visits and telephone calls, patients can initiate calls to the NCM if they require advice and seek help before the next structured activity. The NCM will manage the calls according to the telephone follow-up and referral protocols. The content and duration of the calls will be documented.

### Training program for nurse case managers and volunteers

#### Training nurse case managers

The NCMs already have 6 years of clinical experience in palliative and/or HF care and have completed the post-registration specialty course. They have participated in a training program to enable them to master the key elements of the HPHP and enhance their relevant knowledge and skills (see Additional file 2). The training program was delivered by the research team in partnership with experienced clinical experts.

### Training volunteers

Volunteers are final year nursing students from a local nursing school, who have completed a 9-hour training program including theory- and practice-based content [39]. The training program was delivered by the research team.

### Pre-discharge phase

#### Assessment

Before the patient is discharged, the NCM will conduct a pre-discharge interview with the patient and family. The NCM will discuss the patient’s current physical, psychological, social, and spiritual status with the patient and family, as well as their preferred care approach. The patient and family will be encouraged to ask questions and to express their views throughout the process. At the end of the interview, the NCM will convene to develop a care plan in accordance with the wishes of the patient and family. Upon patient discharge, the nurse will meet with the patient and family to explain the HPHP arrangements and to document the assessment and plan using the Omaha System, which encompasses a comprehensive assessment, intervention, and evaluation scheme [57].

### Post-discharge phase

The first month post-discharge will include weekly care support: week 1 - the NCM and nursing students conduct a home visit together; week 2 - the NCM makes a telephone follow-up call; week 3 - the nursing students conduct a home visit in pairs; week 4 - the NCM makes a telephone follow-up call.

### Second and subsequent months post-discharge

The NCM will provide a monthly home visit, supplemented by a social visit and a telephone follow-up by nursing students each month. The patient will receive the HPHP for up to 12 months.

### Outcome measures

Data for the outcome measures will be collected at five time points: at discharge and at 1, 3, 6, and 12 months post-discharge. A research assistant with no clinical association with the patients will be responsible for collecting the data. In order to ensure the quality of the data collected, the research assistant will be trained in using different data collection tools. A value of 10 % will be used to test the intra-rater reliability, which involves the assistant collecting the same set of data twice within a short interval of time. All the data is independently checked by a member not involved in data collection to ensure the quality of the data collected. All data will be stored in a locked cabinet and will be entered in encrypted files to ensure data protection.

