**Methods/design:**

This is a randomized controlled trial taking place in hospitals in Hong Kong. We have been recruiting patients with end-stage HF who are identified as appropriate for palliative care during hospitalization, on referral by their physicians. A set of questionnaires is collected from each participant upon discharge. Participants are randomized to receive usual care (customary hospital-based care) or the intervention (HPHP). The HPHP will be implemented for up to 12 months. Outcome measures will be performed at 1, 3, 6, and 12 months post-discharge. The primary outcome of this study is quality of life measured by the Chronic Heart Failure Questionnaire - Chinese version; secondary outcomes include readmission rate, symptom intensity, functional status, and satisfaction with care.

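### The protocol article conflicts on whether the baseline scores are taken before or after allocation and the first HPHP contact

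*Protocol article*

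**What the plan says.** Five parts of the protocol article bear on the order of events.

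- **Outcome measures:** the schedule is given as "Data for the outcome measures will be collected at five time points: at discharge and at 1, 3, 6, and 12 months post-discharge". The Abstract (Methods/design) agrees on timing, "A set of questionnaires is collected from each participant upon discharge", and its next sentence turns to randomization.
- **Recruitment procedures:** "After obtaining written informed consent, a research assistant who is blinded to the treatment assignment conducts a baseline interview". The following sentence refers the reader to the outcome measures section for the self-rated scales.
- **Randomization and blinding:** "Having successfully recruited a subject, the research nurse calls the independent site investigator to open an envelope". Neither a completed baseline nor discharge is named as a condition. Participants and families are stated to be unblinded.
- **Pre-discharge phase, Assessment:** "Before the patient is discharged, the NCM will conduct a pre-discharge interview with the patient and family". A care plan follows, and the HPHP arrangements are explained at discharge. The section on usual care plus HPHP makes the case manager a member of the HPHP core team, and the Discussion says that the intervention starts during the inpatient stay.
- **Use of baseline:** Trial phase says follow-up will be compared with baseline as well as between groups. Data analysis names GEE with group, time and interaction effects for the secondary outcome variables.

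**The concern.** If the first scores are taken at discharge and HPHP has already begun, the baseline in the HPHP arm is a post-allocation measurement. It is self-rated by patients who know their arm, so a blinded data collector does not remove the risk. The CHQ domains include emotional status and mastery, which an interview about symptoms, wishes and care plans could plausibly move.

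Any estimate that subtracts or adjusts for such a baseline gives away part of the effect it is meant to measure. If the early contact helps, the loss is toward no difference, and a real benefit could be understated or missed.

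**Working it through.** **Step 1: the order of events.** Two facts are firm. HPHP content is delivered before discharge (Assessment; Discussion). That content comes from an HPHP team member, so allocation must precede discharge for HPHP patients. The position of the baseline scores can then be read in three ways.

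- *Reading A (Outcome measures with Assessment, literally):* consent, envelope, case manager interview and care plan, scores at discharge. Baseline follows allocation and first contact.
- *Reading B (Abstract, in sentence order):* scores upon discharge, then randomization. No patient could then receive a pre-discharge HPHP interview by allocation, which contradicts Assessment.
- *Reading C (Recruitment procedures, then Randomization and blinding):* consent, baseline interview with the scales, envelope, case manager interview, discharge. This is sound, but it fits Outcome measures only if "at discharge" loosely means an earlier point in the index stay. No section says so.

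The blinding of the assistant does not decide between A and C. Before allocation there is no assignment to conceal, and after it the assistant can be blind while the patient is not.

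**Step 2: which estimates depend on the answer.** Let θ be the true between-arm difference at 4 weeks, δ the shift in the HPHP baseline relative to control caused by allocation or early contact, and b the slope of follow-up on baseline.

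- Raw 4-week comparison: estimates θ.
- Change from baseline: estimates θ − δ.
- GEE group-by-time term with the discharge score as reference time: θ − δ at the 4-week visit.
- Baseline-adjusted comparison: θ − bδ.
- Readmission: taken from hospital administrative systems, does not use the baseline scores, unaffected.

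**Step 3: illustration.** The article gives no figure for δ, so it is set as an assumed fraction of θ, with b = 0.5.

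| δ as share of θ | Change score or GEE interaction | Baseline-adjusted |
|---|---|---|
| 10% | 0.90θ | 1 − 0.5 × 0.10 = 0.95θ |
| 25% | 0.75θ | 1 − 0.5 × 0.25 = 0.875θ |
| 50% | 0.50θ | 1 − 0.5 × 0.50 = 0.75θ |

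For power, Sample size estimation gives 117 per arm, 80% and 0.05. If two-sided, this implies a standardised effect of (1.960 + 0.842) × √(2/117) = 0.366 on the raw score. Assume equal variances and a baseline-to-follow-up correlation of 0.5. Change-score power is then 80% with no shift and 71%, 56% and 29% for the three shifts. Baseline-adjusted power is 90% with no shift and 87%, 81% and 68%.

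At the 25% shift, the effect of the assumed correlation is:

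- Correlation 0.3: change-score power falls from 66% to 43%.
- Correlation 0.75: change-score power falls from 98% to 84%.

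These figures show the mechanism. They do not estimate what happened in the trial.

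**The case against.** The strongest reply is that Reading C is the intended one. Recruitment procedures puts the baseline interview after consent and points to the self-rated scales, the randomization section follows, and the Abstract mentions questionnaires before randomization. "At discharge" may only label the index-admission wave against the four later ones. The flowchart and the SPIRIT file, where the sequence would normally appear, are not shown. Both arms also receive a palliative consultation, so the contrast before discharge may be modest. This stands to the extent that contamination is possible but not shown. It does not remove the conflict: the discrepancy lies between statements the article makes, and is not a detail left to a fuller document.

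A reader might infer three stronger points that the article does not support.

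- *That baseline is taken after allocation.* Recruitment procedures and the Abstract's sentence order point the other way.
- *That randomised patients are removed by discharge destination*, because those "discharged to a nursing home or other institution are excluded". This stands among the eligibility criteria, which Recruitment procedures treats as met before the patient is approached. No removal after randomization is described. Only the wording, which names an event rather than a plan, leaves room for doubt.
- *That the loss can be stated in CHQ points.* The difference of 60.4 versus 52.3 in Sample size estimation comes from another study's quality-of-life result, and the article does not say it was measured on the CHQ.

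It is also fair that no change-score or covariance analysis of the CHQ is specified. However, GEE is the only named method that could apply to the quality-of-life scores over time, and Trial phase does announce comparison with baseline.

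**Conclusion.** The concern holds as an internal conflict over the order of baseline, allocation and first HPHP contact. Followed literally, Outcome measures and Assessment place an unblinded, self-rated baseline after the intervention has begun. Change-from-baseline, baseline-adjusted and GEE group-by-time estimates would then be exposed, most likely toward no difference. That direction assumes the early contact improves scores in the HPHP arm; if it worsened them, the bias would reverse. The size of any shift is unknown, and the percentages above rest on assumed shifts and correlations. The 4-week comparison without baseline and the readmission analysis are not at risk. The point is worth correcting, because the correction is cheap and the dates on file can settle whether there was a problem.

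**What to change.** Reconcile the Abstract, Recruitment procedures, Randomization and blinding, Assessment and Outcome measures to one order: consent, all baseline scales, envelope, then case manager interview.

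Trial status says data collection is in its final stage, so for patients already enrolled:

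1. Compare each baseline date with the envelope date and the first case manager contact.
2. Treat only scores obtained before allocation as baseline.
3. Report the 4-week between-group comparison without baseline as a sensitivity analysis.

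As a minor clarification, state that the institutional-discharge exclusion refers to the planned destination recorded at screening, and that every randomised patient stays in the analysis.

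The cost is wording and a check of records. The downside is that some baselines will be treated as missing, which reduces the precision of baseline-dependent analyses.

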### Primary outcome

The primary outcome is quality of life, which will be measured by an HF-specific scale, the Chronic Heart Failure Questionnaire - Chinese version (CHQ) at 4 weeks post-discharge. The CHQ is one of the most commonly used HF-specific QOL instruments. It was developed by Guyatt et al. [58] in Canada. The tool has 20 items on a 7-point Likert scale measuring four domains: dyspnea, fatigue, emotional status, and mastery. The CHQ has been translated into Chinese and validated [59]. The internal consistency and test-retest reliability are good, with a Cronbach’s alpha of 0.95 and an intra-class correlation coefficient (ICC) of 0.75 [59]. In addition, the quality of life will also be measured by the McGill Quality of Life Questionnaire - Hong Kong version (MQOL-HK), which is a palliative-specific instrument measuring four domains: physical, psychological, existential, and support on a numerical scale from 0 to 10. It has been validated among palliative patients in Hong Kong with good reliability (the ICC is 0.85 (*p* < 0.0001) and the Cronbach’s alpha is 0.83) [60].

### Secondary outcomes

Evaluated health outcomes will be functional status, symptom intensity, and satisfaction with care. Functional status will be measured by the Palliative Performance Scale (PPS). The PPS, developed by Anderson et al. [61] based on the Karnofsky Performance Scale, is a tool specifically designed for palliative patients that reflects the changing physical condition in five aspects: ambulation, activities/evidence of disease, self-care, intake, and level of consciousness. The PPS is a clinical tool commonly used in local settings. The level of physical performance is rated on a scale of 100 (normal) to 0 (death), measured in 10 % decrement levels. The scale has been validated and the inter-rater reliability between doctors and nurses was maintained at .85 with strong kappa values of .97 [62]. The internal consistency is also good, with a Cronbach’s alpha equal to 0.83 [63].

The symptom intensity will be measured by the Edmonton Symptom Assessment System (ESAS). The ESAS assesses nine symptoms: pain, fatigue, nausea, depression, anxiety, drowsiness, appetite, sensation of well-being, and dyspnea, measured on a 0–100 mm visual analog scale (VAS). One extra empty VAS is left for the assessment of a less frequent symptom that may be important for an individual patient. The ESAS is widely adopted locally, and has been found to be a valid, reliable instrument for use among palliative care patients [64, 65]. A local study has also shown that the ESAS can help quantify symptoms and is an independent prognosticator for survival [66].

Satisfaction with care will be measured by the 15-item questionnaire used in the study of Wong et al., with validity confirmed by an expert panel and a reported test-retest reliability of .87 [42].

The service utilization outcome is measured by the hospital readmission rate, length of stay, and emergency room visits. The information will be extracted from the hospital administrative systems.

### Statistical methods

#### Sample size estimation

We estimated the sample size based on the study by Brannstrom and Boman [67], which detected a significant improvement in quality of life (intervention 60.4 versus control 52.3) after the structured palliative home care intervention provided by a multidisciplinary team among heart failure patients. A sample size of 117 for each arm is required to achieve a power of 80 % at a significance level of 0.05. To account for a 20 % attrition rate, 140 subjects for each arm with a total of 280 subjects are needed.

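### 140 per arm with 20% attrition leaves 112 evaluable, not 117, so the sample size gives about 78% power, and its 8.1-point basis is not tied to the CHQ at 4 weeks

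*Protocol article*

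**What the plan says.** The Sample size estimation section of the protocol article takes its planning effect from a single earlier trial of palliative home care in heart failure, which "detected a significant improvement in quality of life (intervention 60.4 versus control 52.3) after the structured palliative home care intervention". It continues: "A sample size of 117 for each arm is required to achieve a power of 80 % at a significance level of 0.05". After a 20% attrition allowance it concludes that "140 subjects for each arm with a total of 280 subjects are needed". It does not state the quality-of-life instrument behind 60.4 and 52.3, the SD, the time of measurement, the cited trial's control condition, or whether the test is one- or two-sided.

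The Primary outcome section makes the Chinese CHQ at 4 weeks post-discharge the primary outcome and describes it thus: "The tool has 20 items on a 7-point Likert scale measuring four domains: dyspnea, fatigue, emotional status, and mastery". It also lists a second quality-of-life instrument, the MQOL-HK.

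Under Usual care, both arms receive a palliative care consultation service, and "Home visits and telephone calls may be provided as part of the customary service if deemed necessary". Under Post-discharge phase, "The first month post-discharge will include weekly care support", made up of two home visits and two calls. The programme then continues for up to 12 months.

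**The concern.** There are two separate issues.

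The first is arithmetic. An attrition allowance has to leave the required number after the losses. If 117 must remain and 20% are lost, the number enrolled is 117 divided by 0.8. Adding 20% to 117 falls short, and the power claim then does not hold under the plan's own attrition figure.

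The second is traceability. The 80% belongs to an 8.1-point difference described only as quality of life. Because the trial uses two quality-of-life instruments, that phrase identifies no scale. Unless the effect is connected to the CHQ, to 4 weeks and to a control arm that already has palliative consultation, a reader cannot say which CHQ difference the trial was built to detect. That would matter most if the result were null.

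**Working it through.** **Inputs.** From Sample size estimation: means 60.4 and 52.3, 117 per arm, power 80%, significance level 0.05, attrition 20%, 140 per arm (280 in total). Equal arms. From Primary outcome: 20 items, 7-point scale. Assumption: two-sided test (a one-sided test is also tried below).

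**1. The plan's own 117.** The difference is 60.4 − 52.3 = 8.1. The usual formula is n = 2(z₀.₉₇₅ + z₀.₈₀)² × SD² / 8.1². With no SD stated, it cannot be run forwards, so it is solved for SD:

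- SD = 8.1 × √(117/2) / (1.960 + 0.842) = 22.1
- standardised difference = 8.1 / 22.1 = 0.366 (0.368 with the t distribution, SD 22.0)

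So 117 is consistent with 8.1 points if the SD was about 22. The choice of SD matters:

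| SD assumed | n per arm for 80% power | Power with 117 per arm |
|---|---|---|
| 15 | 54 | 98.5% |
| 20 | 96 | 87% |
| 25 | 150 | 70% |
| 30 | 216 | 54% |

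Reading 60.4 and 52.3 as percentages would need 588 per arm, so that is not where 117 comes from.

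**2. The attrition step.**

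- As apparently done: 117 × 1.2 = 140.4, giving 140.
- As needed: 117 / (1 − 0.20) = 146.25, giving 147 per arm, or 294 in total.
- Left after 20% loss from 140: 140 × 0.8 = 112 per arm.
- Loss that 140 can bear while keeping 117: 23 / 140 = 16.4%.

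**3. Power with 112 per arm at the implied effect.**

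- 0.3663 × √(112/2) = 0.3663 × 7.483 = 2.741
- power = Φ(2.741 − 1.960) = Φ(0.781) = 0.78

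A one-sided 5% test implies SD 24.9 and a standardised difference of 0.325. Then Φ(0.3251 × 7.483 − 1.645) = Φ(0.788) = 0.78, so sidedness does not alter the result.

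Equivalently, 112 per arm gives 80% power for 8.1 × √(117/112) = 8.3 points on the source scale instead of 8.1.

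**4. Could 60.4 and 52.3 be CHQ scores?** The article does not give the scoring. If items score 1 to 7, an item or domain mean cannot exceed 7, so these values are not means. A 20-item sum runs from 20 to 140, and both values fit; 8.1 points would then be 8.1 / 20 ≈ 0.4 per item. The text neither confirms nor excludes the CHQ.

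**5. Illustration only.** If the true 4-week difference were three-quarters of the implied one, power with 112 per arm would be Φ(0.75 × 2.741 − 1.960) = 54%. At one half it would be Φ(0.5 × 2.741 − 1.960) = 28%. The documents give no source for either fraction.

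**The case against.** A reader might infer that the 80% figure belongs to another scale, a longer exposure and a weaker comparator, so that true power for the CHQ at 4 weeks is far lower. The article does not support this. It says only that the cited gain followed a structured intervention, and gives no duration, time point or control condition. The two means would fit a CHQ sum score.

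The early-exposure argument is not one-sided either. The first month has four weekly contacts, preceded by a pre-discharge interview and care plan, and is the densest part of the programme. Control-arm visits are made only where judged necessary. The 54% and 28% figures describe chosen multipliers, not a measured shortfall.

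The missing SD is something a journal article commonly leaves to the full protocol, and borrowing an effect from the nearest related trial is ordinary practice. Neither counts as an error.

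It can also be said that the 20% is tied to no time point. Follow-up runs to 12 months, and if loss by 4 weeks is no more than 16.4%, at least 117 per arm remain and the 80% holds. That is correct, but it is not what the section says: it offers 140 as the number that covers 20% attrition, and it does not. The attrition arithmetic therefore stands, together with the narrower point that the link from 8.1 points to the primary endpoint is not shown.

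**Conclusion.** The attrition step is wrong as written. With the stated 20% loss, 140 per arm leaves 112, five short of the 117 required, and power at the plan's own implied effect is about 78%, not 80%. This is small: about two percentage points, or a detectable difference of 8.3 instead of 8.1 source-scale points. It assumes equal arms, a comparison of two means, an effect back-solved from 117 and 80%, and the full 20% loss at the primary analysis.

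The section also does not show that the 8.1 points apply to the CHQ, to 4 weeks or to a palliative-care control. That is an unshown link, not a demonstrated mismatch, and no power below about 78% follows from the article.

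**What to change.** Leave enrolment as it is; the Trial status section says data collection is in its final stage. Reword the power statement along these lines: *with 112 evaluable per arm (20% attrition), the trial has about 78% power for a standardised difference of about 0.37 in CHQ at 4 weeks (two-sided 5%)*. Confirm the sidedness when doing so. Then:

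- state that 0.37 is the value implied by the plan's own calculation and was not chosen on CHQ grounds;
- name the scale and SD behind 60.4 and 52.3 if they are on file;
- give the CHQ-point equivalent as 0.37 times the pooled SD of the baseline CHQ, computed without group codes and before unblinding, and note that the 4-week SD may differ.

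The cost is one blinded SD calculation and a reworded paragraph. The downside is that the stated power becomes slightly less favourable. Expressing 0.37 in CHQ points also does not show that a difference of that size is meaningful to patients; it only tells readers what the trial could detect.

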## Background

Heart failure (HF) is a global health issue affecting more than 5 million people in the United States (US) [1] and 14 million Europeans [2]. In Hong Kong, the overall HF ratio per 1,000 people is 0.7, resulting in a total of over 5,000 cases; the new:old case ratio is 2.8:1 [3]. Heart failure is the leading cause of death in the US, accounting for 31.4 % of all deaths and followed by cancer and stroke [4]. In Hong Kong, cancer is still the leading cause of death (30.6 %), but heart disease was ranked second (15.5 %) among the 42,705 deaths in 2009 [5]. The management of HF in recent years has improved, but the mortality rate remains high, with a reported 40 % death rate within the first year after diagnosis [6, 7] and 75 % at five years [8]. Patients with heart failure tend to need more emergency room visits, repeated hospital admissions, and longer lengths of stay [1]. In Hong Kong, around 25–50 % of HF patients are readmitted within 6 months of discharge [9]. The repeated use of services results in increased healthcare expenditures [10, 11], costing US$30 billion a year in the US [1] and GBP 905 million in the United Kingdom [8].

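### The target of 140 per arm leaves 112, not the required 117, after the stated 20% attrition; 147 per arm would be needed (a minor correction)

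*Protocol article*

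**What the plan says.** The Sample size estimation section of the protocol article takes its effect from an earlier study of structured palliative home care in heart failure, with quality-of-life means of "intervention 60.4 versus control 52.3". It gives no standard deviation and does not say whether the test is one- or two-sided. From this it states: "A sample size of 117 for each arm is required" "to achieve a power of 80" per cent, "at a significance level of 0.05". The allowance for loss follows: "To account for a 20 % attrition rate", "140 subjects for each arm with a total of 280 subjects are needed". The article prints no inflation formula and mentions no other allowance. No other section revises the 117, the 20% or the 140.

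**The concern.** An attrition rate is ordinarily a share of the patients randomised. To keep a required number after that share is lost, the required number is divided by one minus the rate. Multiplying by one plus the rate always gives too few, and the printed target looks like the result of that multiplication. If so, the article promises 80% power at 20% attrition for a trial of 280 patients, and the design does not deliver it. At stake is the accuracy of a stated property of the design, and of the sample size statement likely to be carried into the final report, which the article says will follow CONSORT. The conduct of the trial is not at stake.

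**Working it through.** **Inputs**, all from Sample size estimation:
- required evaluable patients per arm: 117
- power: 80%
- significance level: 0.05 (sidedness not stated; two-sided assumed below)
- attrition: 20%
- target: 140 per arm, 280 in total
- difference in means: 60.4 − 52.3 = 8.1 (no SD given)

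**Reproducing the printed target.** 117 × (1 + 0.20) = 140.4, which rounds to 140, and 2 × 140 = 280. This route gives the printed figure. Division does not: 117/(1 − 0.20) = 146.25. The multiplication is therefore an inference from the match, not something the article states.

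**What the target leaves.** 140 × (1 − 0.20) = 112 per arm, or 224 in total. The requirement is 117 per arm, or 234 in total. The shortfall is 5 per arm and 10 in total. This step uses only printed figures and does not depend on how 140 was obtained.

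**Size needed at 20% attrition.** 117/0.80 = 146.25, rounded up to 147 per arm, or 294 in total. As a check, 147 × 0.80 = 117.6, which meets 117, while 146 × 0.80 = 116.8, which does not. The printed target is 7 per arm and 14 in total below this; 14/294 is just under 5%.

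**Attrition that 140 per arm can bear.** 1 − 117/140 = 23/140 = 16.4%.

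**Power with 112 per arm.** Because no SD is printed, the standardised effect has to be back-solved from the article's own 117 and 80%.
- Normal approximation, two-sided 0.05: d = (1.960 + 0.842) × √(2/117) = 0.366, an implied SD of 8.1/0.366 ≈ 22.1. At 112 per arm the expected test statistic is 0.366 × √(112/2) = 2.741. Power is Φ(2.741 − 1.960) = Φ(0.781) ≈ 78.3%.
- Two-sample t-test, two-sided 0.05: d = 0.368, implied SD about 22.0, power at 112 per arm 78.2%.
- One-sided 0.05 with the effect back-solved in the same way: 78.5%.

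The loss of power is thus between 1.5 and 2 percentage points under each variant.

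**The case against.** The best defence of the printed figure is that the 20% may have been meant as an addition to the required number. On that reading 20% of 117 is 23.4, and 140 allows for 23 losses. The arithmetic is then consistent, but the losses tolerated are only 16.4% of those randomised, and a reader who takes the attrition rate in its usual sense is misled. The figure would still need restating.

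A second objection is that the point is too small to raise. This stands in part. Less than two points of power are involved, nothing in the analysis, eligibility or endpoints changes, and the Trial status section puts the study at the final stage of data collection, so the size can no longer usefully be altered. That limits both the weight of the point and the fix. It does not make the statement correct. Nor is this detail left to a fuller document: all three numbers are printed in the article and they conflict.

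A third objection is that the power figures rest on a back-solved effect and an assumed two-sided test. That is true and has to be said wherever 78% is quoted. The shortfall in patients needs neither assumption.

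Two stronger readings are tempting, and the article supports neither.
- A reader might set the 20% against the 40% "death rate within the first year after diagnosis" in the Background and infer that 20% can apply only to the earliest visit, with power at 12 months far lower. The 40% describes heart failure generally and is counted from diagnosis. The trial follows selected end-stage patients from hospital discharge, and the article gives no post-discharge mortality or attrition for them. The sample size section also claims no power for later visits.
- A reader might infer that the calculation belongs specifically to the Chronic Heart Failure Questionnaire at 4 weeks, since Primary outcome names that measure and time. The sample size section names no scale and no time point, and the last paragraph of the Background names readmission as the key outcome. Which outcome the 117 supports is a separate question, which a correction of the inflation should not settle in passing.

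**Conclusion.** The statement is wrong as written. The figures of 117 per arm required, 20% attrition and 140 per arm cannot all hold if attrition is a share of those randomised. The target is 7 per arm (14 in total) below the 147 per arm that 20% attrition calls for, and it would leave 5 per arm (10 in total) too few evaluable patients. At 20% attrition, power is about 78% instead of 80%, given a two-sided 0.05 test and an effect of about 0.37 SD implied by the article's own 117 per arm at 80% power. This takes 117 as correct, which cannot be checked without the SD. Multiplication by 1.2 is the likely cause but is inferred. This is a minor correction. It does not threaten the trial, and it says nothing about power at later visits or about which outcome scale the calculation serves.

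**What to change.** Correct the inflation sentence without enrolling more patients. Suggested content: with 140 per arm, 20% attrition leaves 112 evaluable per arm and about 78% power (two-sided 0.05, standardised effect of about 0.37 as implied by 117 per arm at 80% power); 80% power is kept if attrition does not exceed about 16.4%; preserving 117 per arm at 20% attrition would have required 147 per arm, 294 in total. Use the corrected wording in the final report. The correction should not assign the calculation to a particular scale or visit, because the section does not do so.

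The cost is a sentence or two and a slightly less favourable stated power. Nothing in recruitment, data collection or analysis changes.
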